### Study population

#### Inclusion and exclusion criteria

This study will include adult patients (18 years or older) with incurable cancer (i.e. not having curative treatment options) who have a life expectancy of at least three months. Patients are included when they are diagnosed with lung cancer, breast cancer, colorectal cancer, head and neck cancer, lymphoma, or glioma. Furthermore, patients must be aware of the incurability of their cancer.

Patients are excluded when they have severe cognitive impairments or psychotic behavior (delusions and hallucinations), a poor understanding of the Dutch language (and thereby are not able to complete a Dutch questionnaire), or when they are too ill to participate. Patients are also excluded when they do not have access to the Internet or do not have access to an e-mail address, when their healthcare professional thinks that participation will be too much of a burden because a patient is already participating in other studies, or when they already used Oncokompas before (i.e. as cancer patient awaiting or undergoing curative treatment, or as cancer survivor).

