### Outcome assessment

The primary outcome measure to assess the efficacy of Oncokompas is patient activation. Secondary outcome measures are general self-efficacy and health-related quality of life. Also cost-utility outcomes will be evaluated. Outcome measures will be collected through online questionnaires at baseline (t0), two weeks after randomization (t1), and three months after the baseline measurement (t2).

An overview of the primary and secondary outcome measures is shown in Table 2.

**Table 2 Tab2:** Measurement overview

Aim	Outcome measures	Time point		
	*Instrument*	Baseline (t0)	Two weeks after randomization (t1)	Three months after baseline measurement (t2)
Efficacy				
*Primary outcome measure*	Patient Activation	X	X	X
	*Patient Activation Measure (PAM)*			
*Secondary outcome measures*	Self-efficacy	X	X	X
	*General Self-Efficacy Scale (GSE)*			
	Health-related quality of life	X	X	X
	*EORTC QLQ-C15 PAL*			
Cost-utility				
	Quality-adjusted life years	X		X
	*EuroQol 5 Dimensions (EQ-5D)*			
	Medical costs	X		X
	*iMTA Medical Consumption* * Questionnaire (iMCQ)*			
	Productivity costs	X		X
	*iMTA Productivity Cost Questionnaire (iPCQ)*			

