### Sample size

To demonstrate the presence of an effect on the PAM between t0 and t2 of at least 0.5 standard deviations as statistically significant in a one-tailed test at alpha = 0.05 and a power of (1 - beta) = 0.80, at least 51 participants in each condition will be required at three months follow-up. Anticipating a dropout rate of 25% between t0 and t2 (based on earlier research in this population [38]), 68 participants per condition arm need to be included at baseline (t0). In total, 136 cancer patients will be recruited for this study.

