### Economic outcomes

The cost-utility analysis will be conducted in agreement with the intention-to-treat principle. The incremental cost-utility ratio (ICUR) will be calculated by dividing the differences in total costs (i.e. mean costs in the intervention group minus mean costs in the control group) by the differences in QALYs (i.e. mean QALYs in the intervention group minus mean QALYs in the control group). To calculate total costs from a societal perspective, intervention costs, costs of healthcare (i.e. costs of healthcare use and medication), costs for patients and their families (e.g. travelling costs and help received from family and friends), and costs within other sectors (e.g. productivity losses from paid work) will be included. Also total costs from a healthcare perspective will be calculated, which includes intervention costs and the costs of healthcare.

By multiplying resource use by integral cost prices as presented in the Dutch Health Care Insurance Board (CVZ) guidelines on cost studies, costs of healthcare and costs for patients and their families will be calculated [40]. The friction cost method will be used to calculate costs within other sectors [41, 42].

The time horizon will be set at three months follow-up, and therefore neither costs nor effects will be discounted. QALYs will be calculated by multiplying the EQ-5D utility score by the appropriate time period it accounts for. When data are missing on the costs of healthcare, the costs for patients and their families and the costs within other sectors, measured with the iMCQ and iPCQ cost questionnaires, these will be imputed using multiple imputation. This also accounts for missing data on the utilities measured with the EQ-5D.

Non-parametric bootstrapping with 5000 imputations will be used to obtain 95% confidence intervals around the cost and QALY differences. A cost-utility plane will be plotted for the projection of the resulting pairs of cost and effect differences and a cost-effectiveness acceptability curve will be made to reflect the probability of Oncokompas being cost-effective given different willingness-to-pay ceilings [43]. Sensitivity analyses will be conducted focusing on uncertainty in the main cost factors.

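### The imputation rule for missing utilities and costs makes no exception for death; applied literally, it overstates the QALYs of patients who die before t2

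*Protocol article*

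**What the plan says.** The rule is in the protocol article under Economic outcomes. Where healthcare, family or other-sector costs from the two cost questionnaires are missing, "these will be imputed using multiple imputation". The next sentence extends this to utilities: "This also accounts for missing data on the utilities measured with the EQ-5D". Neither sentence mentions death.

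The surrounding provisions matter:

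- Horizon: "The time horizon will be set at three months follow-up".
- Analysis set: "The cost-utility analysis will be conducted in agreement with the intention-to-treat principle", so patients who die remain in the comparison.
- QALY calculation: "QALYs will be calculated by multiplying the EQ-5D utility score by the appropriate time period it accounts for".
- Measurement times: in Table 2 (Outcome assessment), the row "Quality-adjusted life years" and the two cost rows are marked at baseline and three months only. The two-week assessment collects neither utilities nor costs.
- Population: patients with incurable cancer "who have a life expectancy of at least three months" (Inclusion and exclusion criteria).
- Expected loss: "Anticipating a dropout rate of 25% between t0 and t2" (Sample size). The share due to death is not given.
- Sensitivity analyses: those planned for the economic evaluation address uncertainty in the principal cost items, not death or the missing-data assumption.
- Hospital-record data: the characteristics listed under Sociodemographic and medical data do not include date of death.

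**The concern.** After death a patient's utility is 0 by convention. It is not an unobserved value, so multiple imputation is the wrong tool for that period. All t2 utilities come from survivors, so an imputed t2 value for a patient who has died describes someone alive. The same holds for costs: a full three-month total would be imputed for someone who used resources for only part of that time.

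Survival is one of the two components of a QALY. If post-death time is filled with living utilities, every decedent's QALYs are too high and any survival difference between the arms is removed from the estimate. What is at stake is the denominator of the incremental cost-utility ratio, and with it the cost-utility plane and the acceptability curve. Cost-utility is a stated aim of the trial, and the Discussion hypothesises a QALY gain at acceptable cost.

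**Working it through.** **The plan's own figures.** The article states no QALY, utility, cost or mortality figure, so none can be reproduced for this point. The sample size does reproduce: 0.5 SD, one-tailed alpha 0.05 and 80% power give 50.15 per arm by t-test, rounded up to 51; 51 / 0.75 = 68 per arm; 2 × 68 = 136. It is not in dispute.

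**Inputs from the document.** Horizon T = 0.25 year, so at most 0.25 QALY per patient; 68 patients per arm.

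**Assumed inputs.** Utility u = 0.50 to 0.75, the same at baseline and as imputed at t2; death at fraction f = 0.5 of the horizon; utility constant until death.

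**Step 1: excess per death.**

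- Credited under the literal rule: u × 0.25 = 0.125 to 0.188.
- With utility 0 from death: u × f × 0.25 = 0.063 to 0.094.
- Excess: u × 0.25 × (1 − f) = 0.063 to 0.094 QALY.

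Over a wider grid (u = 0.6 to 0.8, f = 0.25 to 0.75, utility before death either constant or falling linearly to 0), the excess runs from 0.038 to 0.175. It is positive throughout.

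**Step 2: arm means.** Overstatement = mortality × excess. At an assumed 10% mortality this is 0.10 × 0.063 to 0.10 × 0.094, or 0.006 to 0.009 QALY. If all of the 25% dropout were death, an upper bound, it is 0.016 to 0.023.

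**Step 3: arm difference.** Error in (intervention − control) = (mortality in intervention − mortality in control) × excess.

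- Equal mortality and equal utility: error 0.
- Three more deaths in one arm: 3/68 × 0.063 to 3/68 × 0.094 = 0.003 to 0.004 QALY, favouring the arm with more deaths.
- A 10-point mortality difference, with u = 0.6 to 0.8 and death halfway under either pre-death assumption: 0.0075 to 0.015.

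**Step 4: utility gain in survivors, equal mortality.** An assumed gain of 0.05 at t2, by linear interpolation, is worth 0.5 × 0.25 × 0.05 = 0.00625 QALY. With 10% mortality in both arms and no gain in those who die, the true difference is 0.9 × 0.00625 = 0.0056. Imputing the gain to decedents reports 0.00625.

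**Step 5: scale.** Assuming a utility SD of 0.20 to 0.25 and a t0–t2 correlation of 0.5, the SD of the QALY is 0.125 × SD × √3 = 0.043 to 0.054. The standard error of the difference at 68 per arm is that × √(2/68) = 0.007 to 0.009. The three-death shift is therefore roughly a third to a half of one standard error, and about half to two-thirds of the 0.006 QALY in step 4.

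**Costs.** No cost figures are given. Imputation adds cost for time after death, but costs before death may differ from survivors' costs in either direction, so the sign of any error is unknown.

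**The case against.** The strongest reply is that the article never classes a death as missing data. A utility known to be 0 is not missing, and the sentence "QALYs will be calculated by multiplying the EQ-5D utility score by the appropriate time period it accounts for" leaves room to stop the clock at death. Handling of deaths is also the kind of detail that a condensed article leaves to an analysis plan, which is not shown. This part stands: it cannot be said that deaths will be imputed, only that the rule as written does so if followed literally. It does not remove the point. The article states an unqualified rule, the QALY sentence does not mention death, and imputation is the only method named for absent follow-up data.

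Three stronger readings are tempting, and the document does not support them:

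- A reader might infer that the arm difference is necessarily biased. Step 3 shows zero error when mortality and utility are equal in the arms. No survival effect is hypothesised. At an assumed 10% mortality, the SD of the between-arm difference in deaths is √(2 × 68 × 0.1 × 0.9) = 3.5, so a gap of three is within chance.
- A reader might infer that entry prognosis equals the length of follow-up. Three months is a floor. The article also restricts the study to patients before the terminal phase and excludes those whose illness is too severe to take part. Deaths before t2 are plausible, but no rate can be derived.
- A reader might infer that a decedent's QALY is fully known, so that no imputation is needed. Only the part after death is known. Utility and costs between t0 and death go unobserved and still need estimation.

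**Conclusion.** The point holds as a defect in a stated rule for the secondary cost-utility analysis. Applied literally, multiple imputation of all missing utilities and costs overstates QALYs for every patient who dies before t2. The size is about 0.06 to 0.09 QALY per death, given an assumed utility of 0.50 to 0.75 and death halfway.

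Bias in the QALY difference and the cost-utility ratio is possible but conditional: it needs unequal mortality or a utility gain in survivors, and its direction is not fixed. Its actual size cannot be determined, because mortality, utility levels and timing of death are not given; nor can any cost bias. The primary outcome and the sample size are unaffected, so this is not a must-fix for the primary analysis. It should be settled before the economic analysis is run.

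**What to change.** State in the analysis plan, or confirm if it already says so, that:

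- the date of death is recorded on the existing case report form;
- utility is 0 and no costs accrue from that date, within the three-month horizon;
- multiple imputation is restricted to time alive. For survivors, this means a missing questionnaire. For decedents, it means only the unobserved utility and costs between t0 and death, with the assumed course of utility up to death stated;
- the number of deaths before t2 is reported by arm beside the cost-utility results.

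The cost is one extra data field, a paragraph in the analysis plan and slightly more analysis work.

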## Discussion

This study among patients with incurable cancer will assess the efficacy of the eHealth self-management application Oncokompas on patient activation, general self-efficacy and health-related quality of life, and its cost-utility from a healthcare and societal perspective, compared to care as usual.

Patients with incurable cancer often have unmet needs and prefer to stay in charge of their own life as long as possible. Therefore, it is important that these patients know where to go for advice and guidance. Oncokompas is developed to support patients to adopt an active role in managing their own health and healthcare. By improving patient activation and self-efficacy, Oncokompas could be a solution to meet patients’ palliative care needs. It provides information and advice to empower patients to take better care of themselves and, when necessary, information on where they can find professional help. By improving the provision of support or facilitating patients to find support, eHealth reduces patients’ needs for support [12, 44]. Due to increasing healthcare costs, an essential advantage of eHealth is its cost-saving potential [23]. Oncokompas is based on the stepped care principle, meaning that the application supports patients to undertake actions to control their symptoms, only with professional care if needed. Therefore, it is hypothesized that Oncokompas will improve QALYs at acceptable costs compared to care as usual.

Oncokompas could stimulate patients to discuss symptoms or questions with their healthcare professional that otherwise would remain unmentioned. Previous studies showed that for instance sexuality issues or concerns about the end-of-life are difficult to address for both patients and their healthcare professionals [45–48]. In addition, consultation time is often short, which hampers addressing all relevant issues that a patient might want to discuss [26]. Oncokompas could also help patients to discuss their symptoms with their healthcare professional in a more structured way (e.g. because they might be more aware of their symptoms and also have the possibility to print their results and take this print to their healthcare professional). Another advantage for patients is that they can use Oncokompas at their own home in their own time.

Since Oncokompas includes topics about decisions at the end-of-life, the application could stimulate patients to think about their wishes regarding the end-of-life (e.g. treatment goals or their preferred place of death) and to talk about this to their family, friends, and healthcare professionals. Therefore, Oncokompas has the potential to contribute to the process of advance care planning (ACP). ACP is the process of discussing patients’ preferences concerning their healthcare, so that they receive the end-of-life care they desire [49]. Research showed positive effects of ACP on the quality of care at the end-of-life [49, 50]. ACP could also have a positive effect on the continuity of care (i.e. the information exchange between healthcare professionals to realize optimal integrated care) during the end-of-life. In its turn this is associated with higher quality of care and lower healthcare costs [51, 52].

In three previous studies on Oncokompas among patients diagnosed with glioma, breast cancer, and head and neck cancer, patients reported that they expected that Oncokompas would stimulate them in taking control and acting upon their symptoms [26, 53, 54]. In addition, one of these studies showed that breast cancer survivors’ activation level was significantly higher after using Oncokompas than before [54]. In 2016 a large RCT started to determine the efficacy of Oncokompas on patient activation and cost-utility among cancer survivors [55]; this study is still ongoing.

To summarize, there is a growing interest in eHealth to improve self-management among patients with chronic disease to emphasize the central role of patients in the management of their own disease and to reduce healthcare costs. This study could contribute to the evidence about the effectiveness of tailored eHealth interventions supporting self-management used in palliative care. When the results of this study show that Oncokompas is effective for patients with incurable cancer, this means that the application supports self-management among these patients. This might improve sustainable implementation and maintenance of the application in advanced cancer care.

## Trial status

This study is still ongoing. The recruitment of patients for this study started in January 2019 and is expected to be complete in June 2020. No publications containing the results of this study have been published or submitted to any other journal.

## Data Availability

The datasets analyzed during the current study will be available in the EASY repository of DANS-KNAW after completion of the thesis that will be written reserving the generated data. The (intellectual) property rights with regard to the generated data will reside at the Vrije Universiteit Amsterdam. Interested parties can request a non-exclusive license for research and educational purposes. The non-exclusive license may be requested only after the completion of the thesis that will be written reserving the generated data.

## Abbreviations

ACP: Advance Care Planning
CVZ: Dutch Health Care Insurance Board
EORTC QLQ C15-PAL: 15-item European Organization for Research and Treatment of Cancer Quality of Life Questionnaire for cancer patients in palliative care
EORTC QLQ C30: 30-item core European Organization for Research and Treatment of Cancer Quality of Life Questionnaire
EQ-5D: 5-dimension EuroQol questionnaire
ES: Effect Size
GSE: General Self-Efficacy
HRQOL: Health-related quality of life
ICUR: Incremental cost-utility ratio
iMCQ: iMTA Medical Consumption Questionnaire
iMTA: Institute for Medical Technology Assessment
iPCQ: iMTA Productivity Cost Questionnaire
LMM: Linear Mixed Models
PAM: Patient Activation Measure
PROMs: Patient-Reported Outcome Measures
QALY: Quality-Adjusted Life Year
RCT: Randomized Controlled Trial
SPIRIT: Standard Protocol Items: Recommendations for Interventional Trials
